#### 3.3.1. Skinfold thickness.

SFT will be measured at the biceps, triceps, subscapular, and suprailiac skinfolds according to the International Society for the Advancement of Kinanthropometry (ISAK) guidelines [37]. The values will be used to estimate each participant’s FM and FFM using adapted equations [2, 81, 82]. SFT is being collected to be compared against deuterium dilution for validation in this population, so that we can use skinfolds and/or bioimpedance alone in future work.

#### 3.3.2. Total body water.

TBW will be estimated using deuterium dilution [40], using a similar approach and notation related to that used by the International Dietary Energy Consultancy Group (IDECG). Assessment of TBW is integrated into the DLW technique as an intermediary step for calculating carbon dioxide production [40,43].

#### 3.3.2. Fat free mass and fat mass.

The measured BM and calculated TBW will be used to calculate FFM and FM. FFM will be derived from TBW using a hydration coefficient (0.732) [40] i.e., the fraction of FFM comprised of water [40,83,84]. FM will be derived by subtracting FFM from BM and its percentage will also be derived [40]:

$$\text{FFM }(\text{kg})\;=\;\frac{\text{TBW}}{\text{hydration coefficent}}$$
(1)

Thus,

FM (kg) = BM−FFM
(2)

$$∴\text{ FM }(\%)\;=\;\frac{\text{FM}}{\text{BW}}\text{ x 100}$$
(3)

The participants FM percentages will be categorized into 4 categories: under fat, normal fat, over fat, and obese using reference curves [85].

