## 1. Introduction

Adolescence is a transitionary developmental phase between childhood and adulthood that is characterized by changes in body composition such as changes in the ratio of fat to fat-free mass, increase in skeletal mass, as well as changes in primary and secondary sexual characteristics [1,2]. Adolescence offers a second opportunity for rapid growth and development, and the final window to eradicate stunting [3]. During this period, humans gain up to 50% of their adult weight, more than 20% of their adult height, and 50% of their adult skeletal mass [4]. These growth and maturational processes lead to elevated daily energy requirements during adolescence and require a corresponding increase in nutritional intake [5], however these requirements are not always met.

A critical element in formulating health and nutrition policies for adolescents is a clear understanding of their energy requirements and dietary intake [6]. Energy requirements refer to the amount of food energy necessary to balance total energy expenditure (TEE), supporting physical activity as well as growth and development [7]; Torun, 2005). In the past, these analyses relied heavily on survey-based estimates of TEE, daily physical activity, and diet [8]. However, in recent decades, the development of accelerometry to objectively measure daily physical activity, and the doubly labeled water (DLW) method to objectively measure TEE during normal daily life have improved assessments of these key variables, and instruments for recording dietary intake have improved [5,9–12].

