### 1.3. Body composition

Body composition refers to the proportions of fat, muscle, bone, and other tissues that make up an individual’s body mass (BM). The primary components of body composition are fat mass (FM), which includes all fat tissue in the body, and fat free mass (FFM) including muscle, bone, organs, and water [33]. Maintaining a healthy body composition is important for overall health, physical performance, and disease prevention which are influenced by diet, physical activity levels, genetics, and age [34].

Body composition studies are crucial for informing strategic interventions and policies aimed at meeting nutritional needs. However, data on body composition among adolescents, particularly in rural and low to middle-income countries (LMICs), has relied on techniques like anthropometric measurements, e.g., skinfold thickness (SFT), and total body electrical conductivity [35,36]. Anthropometry is a rapid and cost-effective technique for assessing body composition [37], but it is limited in its ability to accurately assess body composition [38,39]. There remains a critical gap in foundational data for adolescents who are experiencing dynamic changes in nutritional needs and metabolism [5].

The use of isotope dilution to measure total body water (TBW) has become one of the main methods for conducting body composition analysis [36,40]. In a model of body composition that includes FM and FFM, water is a crucial component of FFM [41] and because the hydration of FFM remains relatively constant among healthy individuals [42], FFM can be calculated from TBW measurement with deuterium dilution [43]. Since deuterium is one of the isotopes used in DLW assessments of energy expenditure, deuterium dilution assessment of TBW and FFM is a standard output for DLW analyses.

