### 1.5. Nutritional challenges in Nigeria

There are approximately 600 million adolescent girls (aged 10–19) worldwide, with nearly 90% residing in developing nations [59]. In Nigeria alone, the number exceeds 25 million, representing about 13% of the total population [60,61]. Adolescents worldwide face numerous nutritional challenges that impact their growth, development, and future health. Undernutrition, micronutrient deficiencies, poor dietary practices, and food insecurity are prevalent in low and middle-income countries (LMICs). Increasingly, these issues coexist with rising obesity rates in LMICs, a phenomenon known as the dual burden of malnutrition [62].

A considerable number of adolescent girls across Africa suffer from chronic malnutrition, severely affecting their health and development. In Nigeria specifically, about 1 in 4 adolescent girls (ages 15–19) are malnourished, and 61% are anemic [63]. Despite these alarming statistics, in Nigeria, similarly to most developing countries, nutrition initiatives have primarily focused on young children and/or adult women, leaving this demographic quite neglected [64]. This neglect is concerning because adolescent girls are particularly vulnerable to malnutrition due to their increased need for nutrients, cultural influences that affect their eating habits, and susceptibility to environmental influences prevalent in impoverished regions [65,66]. Addressing their nutritional needs is a crucial step toward breaking the cycle of intergenerational malnutrition, chronic diseases, and poverty [67]. However, solving these challenges and improving adolescent girl nutrition requires accurate and reliable measures of daily energy needs.

NARN’ia aims to conduct the most comprehensive assessment of energy requirements in adolescent girls in Nigeria to date. This study will integrate dietary assessments using the 24-hour recall method; physical activity levels using accelerometry; anthropometric evaluations of body composition, and the DLW method for assessing both body composition as well as indirect calorimetry. Together, these methods will provide evidence-based data essential for formulating appropriate nutritional guidelines to support healthy growth and development of adolescent girls in Nigeria. Furthermore, this research initiative will establish a foundational framework for future studies on energy requirements in Nigeria and other LMICs.

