### 2.2. Study participants

The NARN’ia study is being conducted in Ikwuano Local Government Area of Abia State, located in southeast Nigeria. Ikwuano is a rural region primarily inhabited by crop farmers and traders from the Igbo ethnic group. The recruitment goal for the NARN’ia study is a total of 70 adolescent girls selected from four secondary schools in Ikwuano. The schools were selected in consultation with local education authorities based on geographic spread, accessibility, school size, and willingness to participate. Within each selected school, eligible participants are identified. From this pool, students are randomly selected through balloting without replacement.

Inclusion criteria include female students between the ages of 10 and 19 years who provide verbal assent and have written parental consent. Exclusion criteria include students with physical disabilities, those who are ill during the study period, and students attending boarding schools due to their more restricted living conditions.

Due to logistical constraints particularly the delayed and phased delivery of research materials from Duke University to the study site at MOUAU, the study is being conducted in two phases. This phased approach also allows the local team to manage recruitment and data collection more effectively. Importantly, both phases follow the same recruitment procedures, inclusion and exclusion criteria, and data collection methodology to ensure consistency and comparability of results.

In Phase 1, which took place in early 2024, 40 participants were recruited from four secondary schools. In Phase 2, an additional 20 participants are being recruited beginning in early 2025. In both phases, the same types of data are collected, including anthropometric measurements (height, weight, body composition), assessments of physical activity levels, and 24-hour dietary recalls. There are also no methodological differences between the two phases.

The study team has also considered the potential influence of seasonal factors, such as school holidays and variations in food availability and physical activity patterns, particularly between the dry and rainy seasons in Nigeria. While both phases are scheduled to occur during the school term to ensure access to participants and minimize variability due to holidays, possible seasonal differences in food consumption and activity patterns will be documented and statistically accounted for in the final analysis.

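### One hydration coefficient of 0.732 is applied to all girls aged 10–19 without a justification for age, and any departure from it passes in full into fat mass

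*Protocol article*

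**What the plan says.** The population is "female students between the ages of 10 and 19 years" (Section 2.2). Total body water (TBW) is measured by deuterium dilution. In the section on fat free mass and fat mass, "FFM will be derived from TBW using a hydration coefficient (0.732"), with no variation by age. Then "FM will be derived by subtracting FFM from BM", and FM% follows from FM. That section adds: "The participants FM percentages will be categorized into 4 categories", using reference curves whose cut-offs are not printed.

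The reason for a constant is in Section 1.3: FFM can be calculated from TBW "because the hydration of FFM remains relatively constant among healthy individuals". Age and maturation are not mentioned there.

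Section 3.3.1 makes the deuterium result the yardstick for another method: "SFT is being collected to be compared against deuterium dilution for validation in this population". The stated aim is to rely later on skinfolds, bioimpedance or both, without the isotope. Section 2.3 expects to relate TEE to body composition and age, among other variables.

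**The concern.** The coefficient converts a measured quantity (TBW) into every body-composition result from isotope dilution. The article fixes its value, prints the equations and names the outputs, so this is a stated choice and not a detail left to a fuller document.

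The stated reason covers healthy people in general. The study covers a ten-year span of growth, and the article gives no ground for holding the value constant across it. The premise of health is also not secure: Section 1.5 reports that in Nigeria "about 1 in 4 adolescent girls (ages 15–19) are malnourished". Section 2.2 excludes girls who are ill, have a physical disability or attend boarding school, but not malnourished girls.

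Three uses depend on the coefficient:

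- **Fat classes.** A shift of a few points in FM% can move girls who lie near a cut-off.
- **Predictors of TEE.** If hydration varies with age, the error in FFM and FM is correlated with age, which Section 2.3 names as another explanatory variable.
- **Skinfold validation.** An error in the reference would be read as an error of the skinfolds, and would affect the decision to use field methods alone later.

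**Working it through.** The article states no error figure for this step, so there is none to reproduce. The check carries an error in hydration through equations 1–3.

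**Inputs from the article:** coefficient 0.732; FFM = TBW / 0.732; FM = BM − FFM; FM% = 100 × FM / BM, where BM is body mass. Equation 3 prints BW in the denominator; it is read here as BM.

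**Assumed inputs, because the article gives none:** true hydration *h* from 0.72 to 0.77, and true fat fraction *f* from 0.15 to 0.30.

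**Formulas.** True TBW is *h* × FFM, so the estimated FFM is FFM × *h* / 0.732. Therefore:

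- relative FFM error = *h* / 0.732 − 1
- FM% error in points = −100 × (1 − *f*) × (*h* / 0.732 − 1)
- relative FM error = −((1 − *f*) / *f*) × (*h* / 0.732 − 1)

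**Per 0.01 of hydration above 0.732.** FFM: 0.01 / 0.732 = +1.37%. FM%: −0.70 × 1.37 = −1.0 points at 30% fat, and −0.85 × 1.37 = −1.2 points at 15% fat.

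**Leverage on FM.** The multiplier (1 − *f*) / *f* is 0.80 / 0.20 = 4 at 20% fat and 0.85 / 0.15 = 5.7 at 15% fat.

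| Assumed *h* | FFM error | FM% error, points (30% to 15% fat) | Relative FM error (30% to 15% fat) |
|---|---|---|---|
| 0.72 | −1.6% | +1.1 to +1.4 | +3.8% to +9.3% |
| 0.732 | 0 | 0 | 0 |
| 0.74 | +1.1% | −0.8 to −0.9 | −2.6% to −6.2% |
| 0.75 | +2.5% | −1.7 to −2.1 | −5.7% to −13.9% |
| 0.76 | +3.8% | −2.7 to −3.3 | −8.9% to −21.7% |
| 0.77 | +5.2% | −3.6 to −4.4 | −12.1% to −29.4% |

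**One girl (assumed 40 kg, 20% fat, *h* = 0.76).** True FFM is 32.0 kg. Estimated FFM is 32.0 × 0.76 / 0.732 = 33.22 kg, which is 1.22 kg too high. Estimated FM is 6.78 kg, so FM% reads 16.9 instead of 20.0. A skinfold estimate that was exactly right for her would appear to overstate FM% by 3.1 points.

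**Age pattern (illustration only).** If hydration fell from an assumed 0.77 in the youngest to 0.732 in the oldest, girls who all truly had 20% fat would read 15.85% at one end and 20.0% at the other, a spurious gap of about 4 points.

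**TEE.** The coefficient enters only equation 1, after TBW. The section on total body water uses TBW itself as the intermediate step to carbon dioxide production, so TEE does not depend on 0.732.

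**The case against.** The strongest objection is that the documents contain no hydration value by age. They do not say that true hydration in these girls exceeds 0.732 or that it falls as they mature, and the sources cited for the coefficient are not at hand. This stands. A reader might infer that the constant certainly overstates FFM and understates FM, most of all in the youngest. The documents do not support that: the direction follows from the assumed *h*, and at 0.72 it reverses.

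Further limits also stand:

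- The Introduction speaks of "changes in body composition such as changes in the ratio of fat to fat-free mass". That ratio can change while the water fraction of FFM stays fixed, so the article does not contradict itself here.
- A reader might infer that the lowest fat class is inflated. Neither the cut-offs nor the distribution of FM% is shown, so no reclassification can be counted.
- A reader might infer that new equations will be fitted to the deuterium result, or that bioimpedance is validated against it. Section 3.3.1 specifies a comparison for skinfolds only, with adapted existing equations, and names bioimpedance only for later use.
- Section 2.3 names body composition as a variable to relate to TEE but fixes no model, so FFM or FM as a predictor is a likely reading and not a stated one.
- Age-specific coefficients also need a source, and their fit to rural Nigerian girls would have to be argued. This is a reason to show both sets of results.

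It can also be said that FFM can be recomputed at any time from the stored TBW. That makes the change easy, but it does not supply the missing justification.

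**Conclusion.** The concern holds in conditional form. The article fixes one coefficient for ages 10–19 on a rationale that is silent on age and maturation, and it derives FM by subtraction, which magnifies any error.

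The sensitivity is exact arithmetic. The size of any actual bias is not known from the documents: 0.8–4.4 points of FM% too low rests on an assumed hydration of 0.74–0.77 with true fat of 15–30%, and 1.1–1.4 points too high rests on an assumed 0.72. If hydration varies with age in this range, the error is age-related and carries into the fat classes, into any use of FFM or FM as a predictor, and into the skinfold reference. If hydration really is 0.732 throughout, there is no bias. The TEE estimates are safe in either case.

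This is a worthwhile, inexpensive improvement to the body-composition analysis.

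**What to change.** Derive FFM, FM, FM%, the fat classes and the skinfold comparison with age- and sex-specific hydration coefficients applied at each girl's age. Cite their source and say why they suit this population. Report the same results with 0.732 alongside, and state whether the fat classes and the skinfold agreement change. Where FFM or FM is used as a predictor of TEE, fit the model with both versions.

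The cost is a look-up by age in an existing calculation. TBW and age are already collected, so no new measurement is needed. Section 5 describes Phase 2 data collection as ongoing and the final analysis as still to come, so the change can be written down beforehand. The small downside is less direct comparability with reports that use 0.732, which the parallel run covers.

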## 4. Discussion

Adolescence marks a crucial phase characterized by rapid physical growth, maturation, and dynamic changes in body composition. This developmental phase, bridging childhood and adulthood, is pivotal for establishing lifelong health trajectories. The prevalence of malnutrition among adolescent girls in Nigeria underscores the urgent need for targeted nutritional strategies that meet their developmental needs. NARN’ia employs a multifaceted approach to comprehensively evaluate energy expenditure, physical activity levels, and body composition to provide the holistic understanding that is needed to inform nutritional interventions. The use of DLW method represents a significant advancement in measuring energy expenditure in this region, contributing novel insights into their energy metabolism and nutritional requirements. Furthermore, the integration of accelerometry for assessing physical activity will address the challenge of quantifying daily activity patterns in this population to offer a more robust measure of TEE.

The insights generated from NARN’ia have significant implications for policy makers and stakeholders involved in adolescent health and nutrition. By outlining precise energy requirements and nutritional patterns among adolescent girls in Nigeria, our findings will inform evidence-based policies aimed at addressing nutritional deficiencies. In summary, this study represents a pioneering effort to comprehensively assess energy requirements among adolescent girls in Nigeria. By addressing gaps in current knowledge and methodologies, our research will contribute valuable data to global efforts aimed at improving nutritional interventions and promoting healthy development during adolescence and guiding future research focused on improving the nutritional status and overall well-being of adolescent girls worldwide.

## 5. Trial status

Data collection for Phase 1 of this study was completed in May 2024, and preliminary data analysis is currently underway. Recruitment for Phase 2 has been completed, and data collection is actively ongoing. The study remains on track for final analysis and dissemination following the completion of both phases.

## Abbreviations

BM: Body mass
BMI: Body mass index
DLW: Doubly labeled water
FM: Fat mass
FFM: Fat free mass
HIC: High income countries
IDECG: International Dietary Energy Consultancy Group
INDDEX: International Dietary Data Expansion
ISAK: International Society for the Advancement of Kinanthropometry
LMIC: Low and middle income countries
MOUAU: Michael Okpara University of Agriculture, Umudike
SFT: Skinfold thickness
TBW: Total body water
TEE: Total energy expenditure
WHO: World Health Organization
